#### Intervention management system

Based on the assessed needs, the Family Care Specialists develop an individualized action plan and implement it in collaboration with various healthcare and social services providers operating within the PlwD’s home environment.

The implementation of the intervention is supported by a computerized IMS, a rule-based expert decision support tool to help Care Specialists in identifying PlwD’s and caregiver’s unmet needs and selecting suitable interventions. Via predefined algorithms and based on PlwD’s and caregiver’s responses to predefined questions from the needs assessment, the system will automatically identify unmet needs and suggest appropriate interventions to address these needs, all summarized in a generated intervention task list. It also supports the intervention monitoring. The IMS draws upon components from prior trials, including the DelpHi-MV [18], Independent [19] and GAIN trial [20]. For *living@home*, the IMS system was further developed by integrating dyad-specific modules and revising all intervention recommendations through multiple expert rounds involving healthcare and nursing scientists, clinicians, and Care Specialists.

#### Mobile health app

An additional key component of the intervention is the mobile health application, which is available to all participating caregivers. The app is used to execute repeated short assessments of the stability of the care situation and the caregiver burden, based on which the dyads are stratified into three intervention intensity levels. This ensures that dyads with a higher caregiver burden or less stable care arrangement receive more intensive support from the caregivers. Also, the level of strain determines the recurrence of the app assessments: dyads in the low-strain group are re-assessed via the app quarterly, while dyads in the moderate and high-strain groups are re-assessed monthly. Besides the tool for repeated assessment, the mobile health app contains several functionalities, such as a chat feature for messaging between the caregiver and the Family Care Specialist, a caregiver diary to capture health and life events, a digital library containing educational materials provided as videos, information text with links that help to address existing unmet needs, and a regional location guide for dementia-related support services.

### Criteria for discontinuing or modifying allocated interventions {11b}

Since the intervention is individualized, its implementation may differ between dyads. However, modifications will be made in specific circumstances: if the caregiver dies, the intervention may be adapted to involve a new caregiver, or the PlwD may continue participation independently. If the PlwD dies, the study will be discontinued for the caregiver. The same procedure applies if either member of the dyad withdraws consent.

### Strategies to improve adherence to interventions {11c}

The intervention is individualized to the dyad’s needs and delivered collaboratively. Continuous access to the intervention and the mobile health app allows caregivers to seek timely support, advice and assistance, promoting engagement and sustained participation. The app’s interactive features—such as regular assessments and direct communication—are designed to foster commitment to the intervention and reduce attrition.

### Relevant concomitant care permitted or prohibited during the trial {11d}

The intervention is subsidiary to usual care. Therefore, all forms of routine medical treatment and psychosocial care available within the German healthcare system will be permitted during the trial. No specific treatments are prohibited.

### Provisions for post-trial care {30}

No specific post-trial care is planned, given the non-invasive and low-risk nature of the intervention. The total study period, during which interventions will be conducted for dyads, is 30 months. During this time, dyads entering the study early may continue to use the app and remain in contact with the informal-caregiver expert after the official 12-month intervention period.

### Outcomes {12}

Primary and secondary outcomes will be assessed at baseline and 12 months after baseline by qualified study nurses not knowing the group assignment via face-to-face interviews and by caregiver self-assessments at the participating memory clinics, allowing for blinded assessment. Furthermore, baseline assessments will be conducted before randomizing dyads to the intervention or control group, also supporting blinding.

#### Primary outcome

The primary dyadic outcome is the caregiver’s self-assessment of the stability of the home care arrangement (Perseverance Time Scale) [11, 21]. Crucial secondary supportive outcomes are the presence, type and severity of neuropsychiatric symptoms of the PlwD (Neuropsychiatric Inventory) [22] and the caregiver burden (Zarit Burden Interview) [23, 24]:i.For the Perseverance Time Scale, informal caregivers are asked (self-assessment) to estimate how long they believe they can continue to provide informal care and, thus, their current care situation. Response options are less than 1 week, less than 1 month, less than 6 months, less than 1 year, less than 2 years, and 2 years or more.ii.The caregivers will also report on the Neuropsychiatric Inventory via face-to-face interviews with a qualified study nurse, providing details about the presence and severity of neuropsychiatric symptoms, including depression, aggression, hallucinations and other behavioral symptoms of the PlwD.iii.The Zarit Burden Interview (12-item version) and ZBI-1 will be used to measure caregiver burden via a self-assessment, measuring physical and emotional strain, social restrictions, financial burden, and perceived effects on caregivers’ health. 

The primary outcome is the stability of the home-based care arrangement, measured by the Perseverance Time Scale which operationalizes the caregivers’ subjective self-estimation of their ability to sustain the current home-based care arrangement. While caregivers’ predictions about future care capacities may be uncertain due to the chronic and progressive nature of the disease, the Perseverance Time Scale is short, easily applicable and well-validated for use in this population. As demonstrated by previous studies with informal caregivers of PlwD, the Perseverance Time Scale showed significant correlations with other burden-related measures, such as the Caregiver Strain Index, the Self-related Burden Scale or the CarerQol-VAS [25]. Changes in caregiver-reported outcomes will be contextualized with concurrent events, such as functional decline of the PlwD, hospitalizations, falls, or other health-related incidents, allowing for a more comprehensive understanding of care dynamics over time.

A crucial secondary supportive outcome is the presence of neuropsychiatric symptoms in PlwD, assessed with the Neuropsychiatric Inventory questionnaire, completed by the informal caregiver via face-to-face interviews with the study nurse. Neuropsychiatric symptoms are well-documented contributors to caregiver burden [26], underlining the dyadic nature of selected primary and crucial secondary supportive outcomes. Caregivers of PlwD exhibiting a higher number of neuropsychiatric symptoms are known to be at elevated risk for emotional and physical strain [27–29] with irritability, agitation/aggression, sleep disturbances, anxiety, apathy, and delusion having the most significant effect on caregiver burden [30]. In the present study, the NPI serves as a standardized outcome measure to quantify behavioral symptom frequency, severity, and associated caregiver distress. Within the intervention, however, behavioral changes are interpreted contextually in relation to the dyad’s care environment. This perspective enables behavioral expressions to inform care planning in a needs-oriented and person-centered manner.

Another crucial secondary supportive outcome is the caregiver burden itself, measured via the Zarit Burden Interview (12-item version), which will be self-completed by caregivers. This tool is among the most commonly applied instruments in informal dementia caregiver research, enabling comparability across studies. While the most commonly used form of the Zarit Burden Interview is a 22-item version, the shortened 12-item version and the 1-item version have demonstrated comparable psychometric properties [23, 24], offering a time-efficient alternative that reduces respondent burden.

#### Qualitative data

In addition to the quantitative analyses, we will conduct guided interviews with experts who are involved in the care process (e.g., physicians in specialized care) to assess facilitators, barriers, acceptance, usability and feasibility of the intervention. In addition, the usability of the Mobile Health App and the Intervention Management System will be evaluated. Interviews will be conducted with *n* = 8 participating dyads, *n* = 8 Family Care Specialists, and *n* = 3 physicians from participating memory clinics. The qualitative data will be evaluated using content analyses by Mayring [31].

#### Further secondary outcomes

A secondary outcome of the study is the caregiver’s resilience, measured by the Resilience and Strain Questionnaire in Caregivers of People with Dementia (ResQ-Care-Dem) questionnaire, which consists of four scales with five items each. Two scales (“My inner attitude” and “My sources of energy”) assess resilience [32, 33]. The other two (“Difficulties in managing the person with dementia” and “General burdens of my living situation”) assess perceived burden. The instrument creates different profiles based on the ratio of burden and resilience factors.

To measure objective stress, hair samples will be analyzed by the University of Konstanz in collaboration with the University of Vienna to assess hair cortisol concentration in caregivers and PlwD, providing a physiological marker of chronic stress [34]. For this analysis, the study nurse will collect two strands of hair from each participant’s back of the head (posterior vertex) at baseline and 12 months later. The strands together should have a diameter of half a pencil, a length of at least 3 cm, and they should be cut as close to the scalp as possible. In addition, information regarding the participant’s hair (e.g., natural color, hair treatments, washing frequency) will be collected via questionnaire. If participants do not consent to the capturing of a hair sample or if their hair is shorter than 3 cm, no samples will be taken.

Another secondary outcome is the caregiver’s self-efficacy measured with the CSES-8 [35]. Self-efficacy means the strength of the caregiver’s belief in being able to complete a specific task. It is a modifiable trait, making it a valuable secondary outcome. The instrument creates a mean score of eight items, with higher scores indicating greater confidence in one’s own caregiving abilities.

A high caregiver burden, less resilience factors and low self-efficacy can lead to depression or anxiety symptoms [36]. Thus, these symptoms will be screened using short versions of the Patient Health Questionnaire (PHQ-2) and the Generalized Anxiety Disorder (GAD-2) tool. Both instruments yield sum scores between 0–6, with ≥ 3 indicating the likely presence of the respective disorder.

As the intervention supports dyads in reducing unmet needs, a secondary outcome is the measurement of unmet needs among PlwD and their caregivers using the Camberwell Assessment of Need for the Elderly (CANE). It consists of 27 categories (including two categories for the caregiver), which assess participants’ needs in various domains. Initially, each of the categories is described (e.g., living situation, household, nutrition, personal hygiene) followed by a question whether the participant has an unmet need in this area (Yes, No) [37]. The CANE is available in two versions: participant and caregiver. If the participant is not able to answer the questions, the caregiver will be asked about the open needs of their relative or caregiver. CANE has been determined suitable for scientific use in dementia and demonstrates appropriate criterion validity [38]. It was easily used by a wide range of professionals without formal training.

#### Process evaluation

The intervention will also be evaluated in terms of acceptance and satisfaction from the perspectives of PlwD, caregivers, and care managers through qualitative interviews within a process evaluation.

#### Claim data analysis

Secondary data, delivered by two participating statutory health insurers, will be used to compare healthcare utilization between dyads being treated at a memory clinic and those receiving care through other institutions (other than memory clinics). The outcomes of this separated analysis of the secondary data—without individual data linkage to primary data—will be the progression of care level for the PlwD and the frequency of mental health problems (ICD-10 diagnoses) for the relatives.

#### Health economic evaluation

For the health economic evaluation, we will measure the dyads’ health-related quality of life by applying the EQ-5D-5L [39] and the EQ-HWB-S [40] as patient and caregiver self-ratings within interviews. The EQ-5D-5L is a widely used, standardized generic instrument that measures the respondent’s health-related quality of life in five dimensions. Responses can be summarized in a health profile that is associated with a health utility index, ranging from zero (death) to one (full health). In combination with the patient’s and caregiver’s life expectancy, the index can be used to calculate quality-adjusted life years (QALYs) for both the patient and the caregiver. The EQ-HWB-9 (EQ Health and Wellbeing short version) is a new generic instrument to measure health and well-being for social care recipients and caregivers and captures a range of health and broader quality of life aspects in seven dimensions.

Healthcare resource use, which is also required for the health economic evaluation, is captured using the Questionnaire for Health-Related Resource Use in an Elderly Population (FIMA) [41] and the Resource Utilization in Dementia Questionnaire (RUD) [42]. These instruments assess the use of medical, formal, and informal care resources, enabling cost calculation from both a payer’s and a societal perspective.

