### Eligibility criteria {10}

Eligible participants are dyads consisting of a PlwD and an informal caregiver. The PlwD must have a formal diagnosis of dementia and reside in his/her own home. The informal caregiver must be the primary caregiver of the PlwD with access to a mobile device with online capabilities. The dyad must reside within the catchment regions of the participating memory clinics to facilitate home visits.

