### Who will take informed consent? {26a}

Participating dyads will receive all relevant information on the study’s objectives, procedures and risks before registration. Both the PlwD and the informal caregiver need to give written informed consent prior to the study. The written study information and the consent form are adapted for the two participating groups; for example, for the PlwD, the forms are reformulated in a simplified format. If the PlwD is unable to consent, their legal representative will be asked to provide written informed consent on their behalf. Physicians in the recruiting memory clinics will be responsible for ensuring the PlwD’s ability to provide informed consent. The original declarations will be kept safely at the respective study center. Participants (and caregivers) will receive a copy. Study participants can withdraw their consent at any time without negative consequences for them. In case of revocation, all personal data of the participant will be anonymized or deleted, if necessary (at DZNE).

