### Methods in analysis to handle protocol non-adherence and any statistical methods to handle missing data {20c}

Missing data will be reported and described in all descriptive analyses. For multivariate analyses, missing data may be imputed using multiple imputation via chained equation, stratified by the respective group, when the missing data are at random.

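### The utility of the person with dementia is taken by self-rating only, with no stated provision for those who cannot answer, so the patient part of the QALY rests on those who still can

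*Protocol article*

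**What the plan says.** Under Health economic evaluation, the protocol article collects the EQ-5D-5L and EQ-HWB-S "as patient and caregiver self-ratings within interviews". It then says of the EQ-5D-5L that "the index can be used to calculate quality-adjusted life years (QALYs) for both the patient and the caregiver". No proxy version of either instrument is named.

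The eligibility section (item 10) sets a diagnosis and a place of residence, with no limit on severity: "The PlwD must have a formal diagnosis of dementia and reside in his/her own home". The consent section (item 26a) provides for people without capacity: "If the PlwD is unable to consent, their legal representative will be asked to provide written informed consent on their behalf".

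A respondent rule for people who cannot answer appears once, for the CANE, under Further secondary outcomes: "If the participant is not able to answer the questions, the caregiver will be asked". The Neuropsychiatric Inventory is informant-based from the start ("The caregivers will also report on the Neuropsychiatric Inventory via face-to-face interviews with a qualified study nurse"), so it is not a fallback for a failed self-rating.

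On missing data, item 20c says that "missing data may be imputed using multiple imputation via chained equation", by group, on condition that the data are missing at random. Item 20a makes the cost per QALY gained the health-economic result, with bootstrapping for its uncertainty.

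**The concern.** The plan expects that some people with dementia cannot answer questions, and deals with this for one instrument. For the instruments that produce the patient utility it names the patient as the respondent and stops there. The trial enrols a progressive disease without a severity ceiling and assesses again after 12 months, so some patients may be unable to self-rate at entry and others may lose the ability by follow-up.

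This gap differs from ordinary missing data in two ways. First, the reason for it, cognitive impairment, is plausibly related to quality of life itself. Second, a proxy rating not collected at the visit cannot be recovered by any later analysis plan. Someone unable at both visits contributes no observed utility, and an imputed value for that person is extrapolated from people who could answer.

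Cost-effectiveness is a stated aim, and the Discussion expects the results to generalise to memory clinics across Germany. The patient part of the QALY would carry that claim less well than the text suggests.

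**Working it through.** **The plan's own figures.** The article gives no figure for utilities or QALYs. Its sample size (item 14) reproduces. With 23% against 35%, two-sided α = 0.05 and 80% power:

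n = [1.96·√(2·0.29·0.71) + 0.842·√(0.23·0.77 + 0.35·0.65)]² / 0.12² = (1.258 + 0.535)² / 0.0144 ≈ 223.3, so 224 per group. Then 224/(1 − 0.175) = 271.5, so 272 per group and 544 in total.

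Item 14 puts total attrition including death at 28%, which leaves 544 × 0.72 ≈ 392 dyads at month 12.

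**Assumed input.** Let m be the share of followed-up patients who cannot self-rate at month 12. The documents do not give it; I use 10% to 40%.

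**Precision.** If only self-raters are analysed, n falls to n(1 − m), and the standard error of the patient utility difference rises by 1/√(1 − m) − 1.

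| m | Patients with a self-rating (392 followed up) | Rise in SE |
|---|---|---|
| 10% | 353 | 5% |
| 20% | 313 | 12% |
| 30% | 274 | 20% |
| 40% | 235 | 29% |

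**Level of utility.** If those unable have a true utility 0.2 lower (assumed), the observed mean is too high by 0.2·m, which is 0.02 to 0.08. With equal shares unable and equal gaps in the two arms, this cancels from the between-arm difference.

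**Between-arm difference.** Assume an effect of 0.03 in those able and e in those unable, with the same m in both arms. The complete-case bias is 0.03 − [(1 − m)·0.03 + m·e] = m·(0.03 − e).

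| m | e = 0 | e = 0.03 | e = 0.06 |
|---|---|---|---|
| 10% | +0.003 | 0 | −0.003 |
| 20% | +0.006 | 0 | −0.006 |
| 30% | +0.009 | 0 | −0.009 |
| 40% | +0.012 | 0 | −0.012 |

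The sign follows e, about which the documents say nothing. If m differs between arms, the level gap no longer cancels and adds a further bias, also of unknown sign.

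**ICER.** Let k be the gain in those unable as a fraction of the gain in those able, with incremental cost held fixed and no imputation. The ratio of true to reported ICER is 1/[1 − m(1 − k)] for patient QALYs alone. If QALYs are summed over the dyad and caregivers contribute an equal gain (assumed), it is 2/[2 − m(1 − k)]. At the extreme m = 40%:

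| k | Patient QALYs only | Patient plus equal caregiver gain |
|---|---|---|
| 0 | 1/0.6 = 1.67 | 2/1.6 = 1.25 |
| 0.5 | 1/0.8 = 1.25 | 2/1.8 = 1.11 |
| 1 | 1.00 | 1.00 |
| 2 | 1/1.4 = 0.71 | 2/2.4 = 0.83 |

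The reported ICER can therefore be too low, correct or too high. The caregiver component pulls every factor towards 1.

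**The case against.** Much can be said for the plan, and several stronger readings do not survive.

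- **Condensed article.** A journal article may leave completion rules to the full protocol. That is fair in general, but here the article does name the respondent for these instruments, and it writes a fallback where it wants one. The point is a stated choice that should be confirmed or changed.
- **Consent and ability to answer.** A reader might infer that everyone enrolled through a representative lacks a utility. Capacity to consent is a different matter from answering a short questionnaire in an interview, and item 41's neighbour in the plan, item 18a, says the data collectors are trained in communicating with people with dementia. The size of the affected group is unknown.
- **Missing at random.** Missingness driven by impairment can be missing at random given recorded severity, and caregiver-reported symptoms could also inform imputation. Item 20b names severity as a possible covariate and subgroup factor. This may reduce the problem, but it does not remove the extrapolation for patients with no self-rating at either visit.
- **The whole QALY result.** A reader might infer that the QALY result as a whole describes milder patients. Caregiver QALYs are also computed and are unaffected.
- **A flattering ICER.** A reader might infer that costs cover all dyads while QALYs cover the milder ones, so that the ICER looks too good. The article does not say who answers the resource-use questionnaires or which dyads enter each part, and the direction depends on an effect pattern that nobody knows.
- **Proxy ratings.** They come from a caregiver who knows the allocation, and the Limitations section already expects favourable reporting by such caregivers. Making the proxy the base case for every patient is therefore debatable.

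**Conclusion.** The point holds in a limited form. As written, a person with dementia who cannot self-rate has no measured utility at that visit, and the patient component of the QALY and ICER rests on those who can, or on imputation from them. Optional imputation under missing at random does not replace a rating that was never taken.

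The certain consequence, for any share unable, is lost precision in the patient component: 5% to 29% on the complete-case standard error for an assumed 10% to 40%. Bias in the between-arm difference is conditional. It needs an effect that varies with severity, or severity-related missingness that differs between arms. The documents support neither a direction nor a size for it, so the ICER factors above are illustrations and not estimates. This is a worthwhile and inexpensive improvement to a secondary economic analysis, and it does not touch the primary outcome.

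**What to change.** 1. Under Health economic evaluation, add the caregiver-proxy EQ-5D-5L for the person with dementia, alongside the self-rating, at baseline and month 12 for dyads not yet assessed.
2. Prespecify which source, self or proxy, feeds the base-case patient QALY. Do not switch source within a person between visits. Report the ICER under the other source as a sensitivity analysis. Either base case can be defended: self-rating avoids an unblinded rater, while the proxy covers more patients.
3. In item 20c, include dementia severity and the proxy rating in the imputation model for missing self-rated utilities.

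The cost is a short amendment and a few minutes of caregiver time at two assessments that already take place. Three limits should be stated. Recruitment began in January 2026, so dyads already assessed have no baseline proxy and need a written rule. No proxy is available where the caregiver has died and the patient continues alone, which item 11b allows. Proxy ratings come from an unblinded caregiver and can differ from self-ratings; the analysis under both sources makes that visible.
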